### Aims and objectives

The aim of this trial, which is part of the Neurotrauma Evidence Translation (NET) programme [48], is to test the effectiveness of a targeted, theory- and evidence-informed implementation intervention to increase the uptake of three key clinical EBCPG recommendations regarding the management of adult patients (18 years of age or older) who present to Australian EDs with mild head injuries, compared with passive dissemination of the EBCPG.

More specifically, the primary objective is to establish whether the intervention is effective in increasing the percentage of patients for which a prospective measure of post-traumatic amnesia (PTA) using a validated tool is performed in the ED until a perfect score is achieved or the patient is transferred or admitted.

Secondary objectives include establishing whether the intervention is effective in: increasing the percentage of patients for which two other assessment methods of PTA were performed (assessment without using tool, and whether the administration of the validated tool was completed at least once); increasing the percentage of patients for which CT scanning is appropriately performed; increasing the percentage of patients who receive patient information upon discharge home from the ED; changing factors that are thought to mediate the effect of the intervention (such as increasing the staff members’ knowledge, or decreasing negative beliefs about consequences); and improving selected patient clinical outcomes and quality of life.

In addition, our study aims to: quantify the trade-off between the hypothesised improvement in patient management and patient health outcomes, and the additional costs (savings) arising from delivery of the implementation intervention and from any subsequent changes in clinical practice and healthcare utilisation by conducting a cost-effectiveness analysis; and evaluate intervention fidelity, assess acceptability of the intervention, and assess perceptions around success of the implementation processes and influencing factors, by conducting a process evaluation.

## Methods/design

The design of this study is a CRT, with the EDs being the clusters including the ED staff members involved in the treatment of patients with mTBI and the patients treated. A randomised design is the preferred one to evaluate the effectiveness of an intervention since it minimises bias in estimating intervention effects compared with other study designs [49,50]. In this study, clusters (hospital EDs) have been chosen for two reasons: the intervention is targeted at the team of ED staff, and EDs represent patient populations in geographical areas, precluding the use of an individually randomised design [51,52].The study has two levels of participation (Figure 1): NET and NET-Plus. NET will measure clinical practice outcomes, but not patient outcomes, whereas NET-Plus will include both. These two options will be offered to hospitals because we anticipate that some may prefer not to recruit patients.

**Figure 1 F1:**
[figure not shown]
**Trial design.** EBCPG, evidence-based clinical practice guideline; ED, emergency department; NET, Neurotrauma Evidence Translation.

### Recruitment and eligibility

#### Recruitment of emergency departments and inclusion/exclusion criteria

The sampling frame for this study will be derived from the Australasian Society for Emergency Medicine ED Directory list of 24-hour Australian EDs (regional and metropolitan) [53]. EDs involved in the pilot and/or development of the intervention will not be invited to participate in the trial.

Hospitals will be included if we receive written informed consent from the ED Director to randomise the ED to control or intervention group. Hospitals will be excluded if they are either non-24-hour EDs or specialised hospitals (for example, women’s or children) and do not therefore routinely treat adult patients with TBI. In addition, EDs will be excluded if they do not have a CT scanner on site, or if there is significant risk of bias (for example, risk of contamination due to two EDs having the same ED Director, or senior influential clinicians working across sites).

We intend to recruit 34 EDs (see sample size section). Based on a previous Australian study ([name], [name], personal communications) which observed a 50% ED participation rate, we plan to initially invite 68 randomly selected hospitals to participate in the trial. Our recruitment strategy will follow recommendations regarding the recruitment for CRTs in secondary care settings [52]. ED directors will be considered ‘gatekeepers’ (people who can grant formal permission for the organisation to be involved) of the clusters. As a first step they will be contacted by telephone to inform them about the study, and let them know that they will receive a recruitment pack (including an invitation letter from the research team, explanatory statement, and an expression of interest form). The ED Director will be encouraged to discuss the trial with the relevant stakeholders within their ED (in particular Directors of Trauma or staff members responsible for trauma and/or research, and senior clinicians). Upon receipt of the expression of interest, a recruitment meeting will be organised (via telephone, skype, video-link or face-to-face) with the study investigators and the relevant stakeholders in the ED. During this recruitment meeting, the details and logistics of the study will be discussed. Following this meeting, the ED Director will be asked to provide written informed consent to trial entry (either NET or NET-Plus), using a consent form sent prior to the meeting [51,52,54]. Non-responders will be followed up by email and telephone [55] at least once, before inviting the next random selection of hospitals.

The content of the recruitment information will be designed to target factors influencing the decision to participate in this trial [56] that were identified in semi-structured interviews in an earlier phase of this study (for example, by providing information around resources and including information around the benefits for the patients to create ‘tension for change’). In addition, professional bodies will be engaged to endorse the trial [57].

#### Recruitment of emergency department staff members for data collection purposes and inclusion/exclusion criteria

ED medical and nursing staff will be invited to complete two questionnaires (at baseline and endpoint). The sampling frame for staff participants will be based on the active list of ED medical and nursing personnel in each ED. Inclusion criteria for nursing staff are: 1) current ED appointment; 2) on active practice roster; 3) enrolled or registered nurses. Inclusion criteria for medical staff are: 1) current ED appointment; 2) on active practice roster; 3) registrars, Hospital Medical Officers or consultants. For both groups, exclusion criteria are: 1) students/interns; 2) clinicians not currently engaged in clinical practice (for example, academic staff); and 3) for nurses, bank or agency nurses.

We plan to randomly select 50 eligible ED clinicians per clinical group per hospital (that is, 100 in total) when available at baseline and endpoint. For hospitals with fewer than 50 clinicians per clinical group, we plan to invite all clinicians satisfying the inclusion criteria to participate for data collection. Staff members who were contacted at baseline will be asked to participate at endpoint, and additional staff will be randomly selected in instances where staff have been lost to follow-up. Staff members will be included if they fit our inclusion criteria and consent to participate.

In addition, some key staff members in eight intervention sites will be recruited to participate in a brief evaluation interview over the telephone. To identify staff, we will use a key-informant method [58].

Finally, all ED Directors or their delegate will be invited to complete two brief checklists over the telephone regarding ED characteristics at baseline and endpoint.

#### Identification of study patients and inclusion/exclusion criteria

In order to determine the effect of the intervention on clinical practice outcomes, a chart audit will be conducted by independent chart auditors. Patients are eligible if they are aged 18 years or older, present to the ED within 24 hours following acute blunt head trauma, and have a GCS score of 14 or 15 at presentation [14]. Exclusion criteria include penetrating injuries, and non-traumatic TBI such as caused by stroke.

A patient identification protocol will be developed and chart auditors will be trained with the aim of maximising consistency in identification of patients, and minimising selective recruitment. We anticipate that patients will be identified retrospectively from clinical records using medical codes (for example, relevant International Statistical Classification of Diseases and Related Health Problems Tenth Revision, Australian Modification (ICD-10AM) discharge codes). Instructions will be piloted and tailored to the hospital medical record system. As there may be some between-hospital variation in the approach taken, the exact process to identify patients will be carefully recorded in each hospital.

#### Recruitment of patients for follow-up – NET-Plus only

In hospitals which choose to participate in NET-Plus, patients included in the chart audit will be contacted by telephone by an ED staff member to invite them to participate in a follow-up telephone interview questionnaire by trained researchers. Informed consent to pass on their contact details to the NET research team will be sought (see ethical review and informed consent).

For this component, additional exclusion criteria are: 1) not consenting to participate in the follow-up study; and 2) not being able to participate in a telephone interview, because of an inability to speak English, being hearing-impaired, or having cognitive or intellectual impairment (history of dementia, other neurological disorder, intellectual disability drug or alcohol abuse or other major psychiatric disorder such as psychosis for which hospitalisation has been required).

These criteria will be confirmed by the ED staff asking for consent and again by the trained researcher at the start of the interview.

### Randomisation and allocation concealment

EDs will be allocated to the intervention and control groups using the method of minimisation proposed by Pocock and Simon [59]. Minimisation has been shown through statistical simulation studies to outperform stratified allocation methods for maintaining baseline balance in prognostic factors [60]. In addition, the method allows for balancing across a greater number of prognostic factors. The minimisation factors will include: the existence of a protocol for mTBI (consistent with our recommendation for appropriate PTA assessment); size (annual presentation rate 2012), included as a proxy for other variables that are harder to measure such as staffing; rurality; and type of participation (NET or NET-Plus). Minimisation is essentially a deterministic method [60], and therefore use of this method can increase the risk of selection bias [61]. We plan to reduce the risk of selection bias through inclusion of a random component and allocation of batches of EDs by a statistician independent of the trial. The statistician will be provided with a file containing only ED codes and the minimisation factors (thus no identifying information). For each batch of EDs, the statistician will randomise the order of EDs before using the minimisation algorithm to allocate the EDs to intervention and control groups.

### Blinding

Due to the nature of the intervention, it will not be possible to blind ED staff members to group allocation. To limit the possibility of selection and detection bias, chart auditors will be independent, where possible, of the hospital. In instances where the hospital does not approve an independent chart auditor, a solution will be discussed which aims to reduce the risk of selectively identifying patients (for example, using a staff member from another unit who will receive training from the research team). External chart auditors and the trial statistician will be blinded to group allocation.

### Interventions

#### Intervention group

Intervention group EDs will receive a targeted, theory- and evidence-informed implementation intervention. The intervention builds upon the previous phases of this study. In phase one, relevant EBCPGs were identified, assessed for their quality, and the focus of the study was determined [11,12]. In phase two, semi-structured interviews underpinned by theoretical perspectives on individual and organisational change were conducted with 42 ED staff members in 13 Victorian EDs. Thematic analysis was used to identify the factors perceived to be influencing current practice as well as change in the ED setting. In phase three, our intervention was developed to address the modifiable influencing factors to maximise the effectiveness of the intervention. Intervention components were piloted for feasibility and acceptability. Table 2 summarises the content of the intervention. Only broad components are described in this protocol to prevent contamination of the control group. The process of development of the intervention and a description of its content will be published in detail post-data collection.

**Table 2 T2:** Planned delivery of the intervention

*Intervention and control group*	
1.	An electronic/printed copy of *Initial Management of Closed Head Injury in Adults* guideline [14].
2.	Data collection reminder sticker/flag in system and education around the importance of documenting information for mild traumatic brain injury patients to optimise data collection.
*Intervention group only*	
3.	One hour face-to-face multidisciplinary stakeholder meeting in each participating hospital with key stakeholders (both clinical and change management) and senior Neurotrauma Evidence Translation (NET) clinicians and researcher to create buy-in at ‘organisational’ level for the changes by discussing the key recommendations and underlying evidence; discussing intervention components and how to overcome anticipated barriers in their implementation etc.
4.	Identification of multidisciplinary local opinion leader team (medical and nursing) via key-informant method [58] (emergency department Directors will be provided with a description of the types and characteristics of people suited to the role).
5.	One day train-the-trainer interactive workshop, led by content experts and senior NET clinicians, attended by the nursing and medical opinion leaders, consisting of information provision and skills training - both in relation to the key-recommendations as well as in relation to their role in the study.
6.	Delivery of materials for local workshops (brief 20 minute sessions) in relation to the key recommendations presented by the clinical opinion leaders to staff in their emergency department over a 3 month period of time.
7.	Provision of relevant tools and materials (for example, screening tools [14] and information booklets [40] translated into five languages that are commonly spoken in Australia).

#### Control group

Control EDs will receive a copy of the EBCPG [14] and all the materials/components needed for the outcome assessment. Post-data collection, control EDs will be invited to a repeat train-the-trainer 1-day interactive workshop where they will also receive the components for the local education and all other intervention materials.

#### Timing of recruitment, intervention delivery, and follow-up

Figure 1 shows the flow of an ED through the trial. We started recruitment and completion of ethics and research governance procedures in February 2013. Baseline data collection has commenced (October 2013). Intervention delivery and endpoint data collection will take place in 2014.

### Study outcomes and outcome measurement

Tables 3 shows our clinical practice outcomes and data collection methods.

**Table 3 T3:** Clinical practice and proxy clinical practice outcomes and data collection methods

	**Method**	**Outcome assessment period/timing**	**Data source**	**Level data collected**	**Analysis level**
**Primary outcome**					
Appropriate post-traumatic amnesia screening (PTA)	Chart audit (retrospective)	2 month period post-intervention	Hospital record	Patient	Patient
**Secondary outcomes**					
** *Clinical practice outcomes* **					
PTA screening tool	Chart audit (retrospective)	2 month period post-intervention	Hospital record	Patient	Patient
Memory - clinical assessment	Chart audit (retrospective)	2 month period post-intervention	Hospital record	Patient	Patient
Computed tomography scan - clinical criteria (CT)^1^	Chart audit (retrospective)	2 month period post-intervention	Hospital record	Patient	Patient
Provision of patient information (INFO)	Chart audit (retrospective)	2 month period post-intervention	Hospital record	Patient	Patient
Safe discharge based on PTA and INFO	Chart audit (retrospective)	2 month period post-intervention	Hospital record	Patient	Patient
Safe discharge based on PTA, CT, and INFO	Chart audit (retrospective)	2 month period post-intervention	Hospital record	Patient	Patient
** *Proxy measures of clinical practice* **					
Self-report of adherence to recommended practice					
• PTA	Staff questionnaire (1-item)	Baseline/Endpoint	Doctors	Staff member	Staff member
			Nurses		
• CT	Staff questionnaire (1-item)	Baseline/Endpoint	Doctors	Staff member	Staff member
• INFO	Staff questionnaire (1-item)	Baseline/Endpoint	Doctors	Staff member	Staff member
			Nurses		
Behavioural simulation^2^ to adhere to recommended practice					
• PTA	Staff questionnaire (clinical vignettes)	Endpoint	Doctors	Staff member	Staff member
			Nurses		
• CT	Staff questionnaire (clinical vignettes)	Endpoint	Doctors	Staff member	Staff member
			Nurses		
• INFO	Staff questionnaire (clinical vignettes)	Endpoint	Doctors	Staff member	Staff member
			Nurses		

^1^Criteria that justify a scan are: age 65 years or older; GCS <15; amnesia; suspected skull fracture; vomiting and coagulopathy (see Additional file 1). ^2^Clinical decision in response to individual simulated patients, for example in patient scenarios.

#### Primary outcome

Our primary outcome is ‘appropriate PTA screening’ (PTA; Table 3). This outcome measures whether a prospective assessment of PTA was appropriately undertaken, where appropriately undertaken is defined as using a validated tool, until a perfect score was achieved (indicating absence of acute cognitive impairment) before the patient was discharged home (or the patient was admitted or transferred). This measure has been chosen as the primary outcome for the following reasons. First, PTA has been shown to have better predictive ability with clinical outcomes compared with GCS [15-18]. Many patients are oriented by the time they are first assessed, and therefore achieve the top score on the GCS scale, which leads to the common misperception that a perfect score means a normal examination [62]. Ponsford and colleagues conceptualised the Revised Westmead PTA Scale for screening of PTA in patients with mTBI, identifying it as more sensitive to the presence of PTA than GCS [63]. Shores and colleagues [17] studied the diagnostic accuracy of the Revised Westmead PTA scale and showed that at the time of the second neurological observation 60% of participants were not able to lay down new memory; yet 87% of them had been assigned a GCS of 15. Another recent study [15] showed that whereas patients with GCS scores of 13 or 14 did not differ from those with a score of 15 with respect to neuroimaging abnormalities, patients who had experienced PTA for more than 30 minutes were more likely to have intracranial abnormalities on imaging. So, by using a validated tool as part of the neuro-observations until patients receive an optimal score, one reduces the risk of failing to classify mTBI patients and prevents patients from being discharged from hospital while they are suffering from acute cognitive impairment [19,20].

Second, this outcome can be reliably measured (the score is an objective measure in the medical records). Finally, given the estimated low rate of appropriate PTA screening (see sample size section), there is considerable opportunity for improvement.

#### Secondary outcomes

##### Clinical practice outcomes

Two other measures for PTA were selected as secondary outcomes. ‘PTA screening-tool’ measures whether the administration of the validated tool was completed at least once. ‘Memory-clinical’ measures whether staff members have made an assessment of memory using questions in their clinical assessment. Other secondary measures assessing the effectiveness of the intervention in improving the ED management of mTBI are listed in Table 3. On the cohort of patients for whom risk criteria are recorded, ‘CT scan-clinical criteria’ (CT) measures whether a CT scan was provided in the presence of a risk factor that justifies the scan (see Additional file 1). This measure is therefore indicating whether a scan was appropriately received; however, we will not be able to measure whether a scan was ‘appropriately denied’ because of the inconsistency in recorded clinical criteria. ‘Provision of patient information’ (INFO) measures whether information was recorded as provided upon discharge home from the ED. Via the chart audit, we will not be able to measure what information was handed out (for example, the information used in our intervention [40] or other). However, this will be assessed in the patient follow-up interview in NET-Plus hospitals. Two measures of ‘safe discharge’ are included, the first being a composite score of PTA and INFO (for all patients), and the second provides a composite measure of whether the patient received appropriate care for all of the three clinical practices (PTA, CT, INFO; for the subgroup of people for whom risk criteria were recorded).

Clinical practice outcomes will be measured retrospectively through chart audit by an independent, trained chart auditor. Data will be collected over the 2 month period following the last intervention component.

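### Entry to the CT outcome and the PTA+CT+INFO composite depends on recorded risk criteria, including amnesia, so these two analysis sets can depend on arm

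*Protocol article*

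**What the plan says.** Under Secondary outcomes, Clinical practice outcomes, the CT measure asks whether a scan was given when a justifying risk factor was present. It is computed "On the cohort of patients for whom risk criteria are recorded". The composite of PTA, CT and INFO is likewise "for the subgroup of people for whom risk criteria were recorded", whereas the composite of PTA and INFO covers all patients. Footnote 1 to Table 3 lists the criteria: "Criteria that justify a scan are: age 65 years or older; GCS <15; amnesia; suspected skull fracture; vomiting and coagulopathy". It refers to Additional file 1, which is not shown.

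Aims and objectives gives the primary objective as "increasing the percentage of patients for which a prospective measure of post-traumatic amnesia (PTA) using a validated tool is performed". Primary outcome describes the Revised Westmead PTA Scale, "identifying it as more sensitive to the presence of PTA than GCS". It cites a study in which "60% of participants were not able to lay down new memory; yet 87% of them had been assigned a GCS of 15". A further secondary outcome, Memory-clinical, "measures whether staff members have made an assessment of memory using questions in their clinical assessment". The chart audit covers the two months after the last intervention component.

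The section on clinical practice outcomes also says that appropriately withheld scans cannot be measured "because of the inconsistency in recorded clinical criteria". It does not say that membership of the recorded-criteria subgroup could differ between arms.

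**The concern.** Whether a patient counts towards the CT outcome or the three-part composite is settled after randomisation, by what staff look for and write down. One of the items they may write down is amnesia, which the intervention is designed to make them test for. The cited example suggests that many patients with amnesia have a GCS of 15, so they would not already qualify through the GCS criterion. If the intervention works on its primary outcome, the intervention arm may gain patients who would have gone unrecorded in the control arm.

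If those patients are scanned at a different rate from the rest, the measured proportion moves even though nobody's scanning behaviour has changed. In the composite, a patient who enters through tool-detected amnesia has by definition had the tool used, so entry is also linked to the PTA component. At stake is the conclusion on one of the three key recommendations and on the fullest safe-discharge measure. Both are secondary outcomes.

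**Working it through.** **Plan's own figure.** The article gives no expected rate for the CT outcome or the composite. The nearest stated figures are in Sample size: 10% against 30% appropriate PTA screening, ICC 0.18, coefficient of variation 0.47, 30 patients per ED. The design effect is 1 + ((1 + 0.47²) × 30 − 1) × 0.18 = 7.41. The unclustered size is (1.96 + 0.84)² × (0.10 × 0.90 + 0.30 × 0.70) / 0.20² = 58.9 per arm. Then 58.9 × 7.41 / 30 = 14.5, which gives the stated 15 EDs, or 15 × 30 = 450 patients per arm. This confirms the inputs but says nothing about the CT analysis set.

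**Illustration.** All of the following are assumptions, and none is a figure from the documents:
- q: share with another criterion, recorded equally in both arms (0.3 or 0.5)
- a: share with true amnesia among the rest (0.2, 0.4 or 0.6)
- s: probability that this amnesia is detected and recorded (0.1 control, 0.3 intervention). The values are borrowed from the screening rates above.
- c1, c0: scan rates in patients with another criterion and in those with amnesia only, identical in both arms

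Denominator share: D = q + (1 − q)·a·s. Measured CT rate: [q·c1 + (1 − q)·a·s·c0] / D.

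Denominators per 450 patients, and the apparent CT difference (intervention minus control, percentage points) when the true difference is nil:

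| q | a | Denominator, control → intervention | c1 80%, c0 40% | 80%, 60% | 80%, 80% | 60%, 80% |
|---|---|---|---|---|---|---|
| 0.3 | 0.2 | 141.3 → 153.9 | −3.1 | −1.6 | 0 | +1.6 |
| 0.3 | 0.4 | 147.6 → 172.8 | −5.3 | −2.7 | 0 | +2.7 |
| 0.3 | 0.6 | 153.9 → 191.7 | −6.9 | −3.5 | 0 | +3.5 |
| 0.5 | 0.2 | 229.5 → 238.5 | −1.5 | −0.7 | 0 | +0.7 |
| 0.5 | 0.4 | 234.0 → 252.0 | −2.7 | −1.4 | 0 | +1.4 |
| 0.5 | 0.6 | 238.5 → 265.5 | −3.8 | −1.9 | 0 | +1.9 |

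Worked example (q 0.3, a 0.6, 80% and 40%): control (0.24 + 0.0168) / 0.342 = 75.1%; intervention (0.24 + 0.0504) / 0.426 = 68.2%.

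**Sensitivity to detection.** With recorded detection of 50% against 60% in the same row, D is 0.510 and 0.552. At 80% and 40% the rates are 63.5% and 61.7%, a difference of −1.8. At 60% and 80% they are 68.2% and 69.1%, a difference of +0.9. A smaller gap in detection shrinks the artefact.

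**Sign reversal with a real benefit.** Take q 0.3, a 0.4, c1 80%, and let detection raise scanning of amnesia-only patients from 40% to 60%. Among all truly indicated patients (share 0.58) the CT rate is (0.24 + 0.28 × (0.1 × 0.6 + 0.9 × 0.4)) / 0.58 = 61.7% in control and (0.24 + 0.28 × (0.3 × 0.6 + 0.7 × 0.4)) / 0.58 = 63.6% in intervention. The recorded-criteria measure goes from (0.24 + 0.0168) / 0.328 = 78.3% to (0.24 + 0.0504) / 0.384 = 75.6%. A real gain is displayed as a loss.

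**The case against.** Several points on the other side have force.

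- **Screening rates are not detection rates.** A reader might take 10% and 30% as the plan's own rates of recorded amnesia. They are not. They describe repeated use of a validated tool until a perfect score, or until admission or transfer. Amnesia can also reach the chart after a single use of the tool or through ordinary memory questions, in either arm, and no rate is given for those routes. This stands, and it makes the range above illustrative only.
- **Direction.** A reader might infer that the extra patients are milder and so drag the intervention arm down. The article does not support that. Its Primary outcome section cites evidence that PTA lasting more than 30 minutes went with more intracranial abnormalities on imaging. The bias may go either way or be nil.
- **Documentation support in both arms.** Table 2, item 2, gives both arms a reminder and education on documenting. This may even out the charting of what staff know. It does not even out who is tested for amnesia.
- **Over-scanning.** A reader might add that an ED that scans everyone would score 100%. That follows from the definition, but the article already discloses that it cannot measure appropriately withheld scans. It is a stated limitation.
- **Unseen detail.** Additional file 1 may define amnesia more closely, and a recorded criterion might mean a positive one or merely a documented one. Either way, recording happens after randomisation.
- **Scope.** These are secondary outcomes, age and presenting GCS should be stable parts of the denominator, the vignettes give a CT measure independent of charts, and a full analysis plan is promised. This limits the weight of the point. The restriction itself, however, is fixed in this document.

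**Conclusion.** The point holds as a caution on two secondary outcomes. Membership of the analysis sets for the CT outcome and the PTA+CT+INFO composite can depend on arm, because one entry criterion is something the intervention leads staff to look for. The mechanism follows from the article's text, but the size and direction do not. Under the assumptions shown, the spurious CT difference runs from −6.9 to +3.5 points, with denominators about 4% to 25% larger in the intervention arm. It vanishes when amnesia-only patients are scanned as often as the others. The composite is exposed to the same selection, but no size was worked out for it.

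A reader might conclude that the denominators differ by design, or that the CT comparison is certainly biased. The documents do not support that. A difference is to be expected only to the extent that the intervention raises recorded amnesia in patients with no other recorded criterion. The primary outcome, INFO and the PTA+INFO composite are not restricted to this subgroup and are not affected.

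**What to change.** In the analysis plan, for both outcomes:

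1. Pre-specify an analysis in patients who qualify on facts ascertained the same way in both arms: age 65 or older, or GCS 14 at presentation. Both are eligibility items in the audit. This is a choice of analysis set and implies nothing about who should be scanned.
2. Report the size of the recorded-criteria denominator by arm.
3. Compare the CT rate in all audited patients by arm. CT receipt is already abstracted from charts (Table 5).
4. State that a change in appropriate CT will not be concluded from the recorded-criteria version unless the fixed-denominator analysis agrees.

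This costs a few lines of wording and no new data. The trade-off is that the fixed set is smaller and leaves out patients who qualify only by amnesia, suspected skull fracture, vomiting or coagulopathy. It therefore answers a narrower question and should sit beside the full-criteria version without displacing it. The all-patient CT rate measures use, not appropriateness, and should be labelled so.
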